### Outcome measures

#### Primary outcomes

The primary outcomes include neuroimaging indicators derived from fMRI, 3D-T1WI, and ASL, specifically: The primary outcome is defined as the change in these multimodal MRI indicators from baseline to the end of the 4-week intervention; the principal comparison is the between-group difference in these changes (taVNS vs. sham-taVNS), with within-group pre-to-post changes assessed as a secondary contrast. The specific indicators are as follows:

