###### Cortical surface area

Cortical Surface Area (CSA) is another important morphometric parameter derived from SBM analysis. It measures the total area of the cortical mantle at each vertex and is closely related to the tangential expansion of cortical columns during neurodevelopment (47). Unlike cortical thickness, which primarily reflects radial growth and dendritic arborization, CSA is thought to be largely determined by the number of cortical minicolumns and is influenced by distinct genetic and environmental factors (48).

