### Data analysis

#### Imaging data analysis

The rs-fMRI data will be preprocessed using SPM12 (https://www.fil.ion.ucl.ac.uk/spm/) and DPARSF 5.0 toolkit (56) with Matlab 2020a. Data preprocessing includes the first ten time points removed to allow for magnetization equilibrium, slice timing correction, realignment for head motion correction (subjects with head motion exceeding 2 mm in translation or 2° in rotation will be excluded), spatial normalization to Montreal Neurological Institute (MNI) space and resampled at 3 mm × 3 mm × 3 mm voxel size, spatial smoothing with a 6 mm full-width at half maximum Gaussian kernel, linear detrending, nuisance covariates regression (including 24 head motion parameters, white matter signals, and CSF signals), and band-pass filtering (0.01–0.08 Hz).

After standard preprocessing, ReHo, ALFF, and fALFF analyses will be calculated to explore regional brain activity. For FC analysis, seed regions will be defined based on brain areas showing significant differences in ALFF, fALFF, or ReHo analyses, and the mean time series of each seed region will be correlated with the time series of all other voxels across the whole brain using Pearson’s correlation coefficients, which will be subsequently transformed to z-values using Fisher’s r-to-z transformation to improve normality (57). Two-sample Student’s t-tests and paired Student’s t-tests will be conducted respectively to examine the differences in taVNS-related central responses between groups and within groups. The results will be corrected by Gaussian Random Field (GRF) Theory (voxel-level *P* < 0.005, cluster-level *P* < 0.05) (58).

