Structural 3D-T1WI data processing will be performed using two complementary approaches. For VBM, the CAT12 toolbox (http://www.neuro.uni-jena.de/cat/) implemented in SPM12 will be employed. Data preprocessing includes bias-field correction, tissue segmentation into GM, White Matter (WM), and CSF maps, spatial normalization to Montreal Neurological Institute (MNI) space using the Diffeomorphic Anatomical Registration Through Exponentiated Lie Algebra (DARTEL) algorithm, modulation to preserve the total amount of tissue within each voxel, resampling at 1.5 mm × 1.5 mm × 1.5 mm voxel size, and spatial smoothing with an 8 mm Full-Width at Half Maximum (FWHM) Gaussian kernel. For SBM, cortical reconstruction and parcellation will be performed using FreeSurfer (ver. 7.2; https://surfer.nmr.mgh.harvard.edu/). The processing pipeline includes motion correction, intensity normalization, skull stripping, automated tissue segmentation, identification of the white matter and pial surfaces, cortical surface inflation and registration to a spherical atlas, and cortical parcellation based on the Desikan-Killiany atlas (59). CT will be computed as the shortest distance between the white matter and pial surfaces at each vertex, and cortical surface area (CSA) will be calculated as the total area of the cortical mantle at each vertex. Surface maps will be smoothed with a 10 mm FWHM Gaussian kernel. Two-sample Student’s t-tests and paired Student’s t-tests will be applied to examine inter-group and intra-group differences in GMV, CT, and CSA, respectively. VBM results will be corrected by GRF Theory (voxel-level *P* < 0.005, cluster-level *P* < 0.05), and SBM results will be corrected using the Monte Carlo cluster-wise correction method (cluster-forming threshold *P* < 0.001, cluster-level *P* < 0.05) (60).

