ASL data processing will be performed using SPM12 and the ASLtbx toolbox (https://www.nitrc.org/projects/asltbx/). Preprocessing includes motion correction of the ASL time series, co-registration to the individual 3D-T1WI structural image, pairwise subtraction between labeled and control images to generate perfusion-weighted images, and quantitative CBF map calculation using the single-compartment model in accordance with the consensus recommendations (61). The CBF maps will then be spatially normalized to MNI space using the transformation parameters derived from the structural image normalization, resampled at 2 mm × 2 mm × 2 mm voxel size, and spatially smoothed with a 6 mm FWHM Gaussian kernel. Two-sample Student’s t-tests and paired Student’s t-tests will be conducted to examine the between-group and within-group differences in regional CBF, respectively. The results will be corrected by GRF Theory (voxel-level *P* < 0.005, cluster-level *P* < 0.05). Across all imaging modalities, these thresholds were applied to control the family-wise error rate; GRF correction was used for the voxel-wise analyses (rs-fMRI, VBM, and ASL), whereas the Monte Carlo cluster-wise method was adopted for the surface-based analyses (CT and CSA) because it is better suited to the geometry of the cortical surface. These criteria follow widely adopted neuroimaging conventions, balancing protection against false positives with sensitivity to true taVNS-related effects.

Additionally, Pearson’s correlation analyses will be performed to explore the relationships between changes in neuroimaging indicators (ALFF, fALFF, ReHo, FC, GMV, CT, CSA, and CBF) and changes in clinical outcome measures (PSQI, NIHSS, ADL, HAMD-17, and HAMA-14), with statistical significance set at *P* < 0.05 (Bonferroni-corrected). For these brain-behavior correlations, the mean values of each neuroimaging metric will first be extracted from the clusters showing significant between- or within-group differences in the preceding voxel- or vertex-wise analyses; these extracted values, rather than whole-brain maps, will then be correlated with the corresponding changes in clinical scale scores. Pearson’s correlation will be applied when both variables satisfy the assumptions of normality and linearity, and Spearman’s rank correlation will be used otherwise. The taVNS and sham-taVNS groups will be analyzed separately, and the Bonferroni method will be used to correct for the number of correlation tests performed.

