Such integrated analyses are expected to identify specific neuroimaging biomarkers that can not only predict treatment responsiveness but also clarify the central mechanisms through which taVNS exerts its therapeutic effects. For example, the association between enhanced functional connectivity in the DMN and reduced PSQI scores may suggest that taVNS exerts its sleep-promoting effects by modulating large-scale neural networks involved in self-referential processing and arousal regulation (70). Similarly, the correlation between increased cerebral blood flow in the thalamus and prefrontal regions and improved sleep maintenance may indicate that the restoration of neurovascular coupling is one of its key mechanisms of action (71). Building on these prior mechanistic findings, we can make several specific predictions regarding the brain regions most likely to be modulated by taVNS in PSI. At the functional level, given that taVNS has been shown to normalize spontaneous activity and to enhance connectivity within the default mode network, thalamus, and prefrontal cortex in primary insomnia and depression (17, 40, 70), we anticipate that the taVNS group will show increased ALFF/fALFF and ReHo in the prefrontal cortex and precuneus, together with strengthened thalamo-cortical and intra-DMN functional connectivity. At the structural level, because chronic sleep deprivation is associated with gray matter atrophy in the hippocampus, prefrontal cortex, and anterior cingulate cortex (24, 25), a 4-week intervention may produce measurable increases, or attenuated loss, of gray matter volume and cortical thickness in these emotion- and cognition-related regions. At the perfusion level, taVNS is expected to increase cerebral blood flow in the thalamus and prefrontal cortex, reflecting restored neurovascular coupling in hypoperfused, sleep-regulating areas. We further hypothesize that these regional changes will correlate with clinical improvement, such that greater enhancement of prefrontal-thalamic function and perfusion is accompanied by larger reductions in PSQI and HAMD/HAMA scores. Specifying these candidate regions and directional hypotheses in advance strengthens the forward-looking value of the protocol and provides concrete, testable targets for the planned analyses.

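### Eight primary imaging metrics are each tested at a cluster-level 5% with no correction across maps, so the stated family-wise error control holds at most within each map

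*Protocol article*

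**What the plan says.** Under Primary outcomes, the protocol article states: "The primary outcome is defined as the change in these multimodal MRI indicators from baseline to the end of the 4-week intervention". The main contrast is taVNS against sham on those changes, and within-group change is secondary. The subsections that follow describe eight indicators: ALFF, fALFF, ReHo and FC from resting-state fMRI; GMV, CT and CSA from the T1 image; and CBF from ASL. None is named as the lead metric, and no testing order or split of alpha is given.

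Imaging data analysis sets the thresholds modality by modality:
- Resting-state metrics: "The results will be corrected by Gaussian Random Field (GRF) Theory (voxel-level *P* < 0.005, cluster-level *P* < 0.05"; the same pair of values is repeated for VBM and for ASL.
- Surface metrics: "SBM results will be corrected using the Monte Carlo cluster-wise correction method", with a cluster-forming threshold of 0.001 and cluster-level P < 0.05.

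The ASL paragraph then sums up: "Across all imaging modalities, these thresholds were applied to control the family-wise error rate". The only adjustment across tests in that section is Bonferroni, for the correlations between imaging change and clinical change.

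FC seeds are to be taken from areas with significant differences in ALFF, fALFF or ReHo.

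**The concern.** Cluster-level correction answers one question: given the many voxels or vertices in this map, how surprising is a cluster this large? It does not account for seven or more such maps being inspected, any one of which would count as a positive primary outcome. A reader who takes the summary sentence at face value would believe that the chance of a false primary finding is held at 5% over the whole imaging programme. It is not.

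The article protects the brain-behaviour correlations, which it presents as exploration, against the number of tests. It gives the primary outcomes no such protection. The Abstract says that the findings will support clinical application of taVNS, so the error rate attached to a positive primary result matters.

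**Working it through.** **Inputs.**
- Primary metrics: eight (Primary outcomes and its subsections).
- Error rate per map: cluster-level 0.05 for every metric (Imaging data analysis). I take this as exactly 5% per map, two-sided; two-sidedness is stated under Clinical data analysis.
- Contrasts counted: one between-group comparison per metric. The secondary within-group contrasts are left out.
- Correlation between metrics: not given in the document, so it is assumed and varied.

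**The plan's own figure.** One map gives 1 − 0.95 = 5%. The stated threshold is therefore reproduced for a single map. The article gives no overall rate across maps.

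**How many maps can give a first false positive.** Suppose no metric truly differs between groups or changes within groups (the global null). FC then runs only after ALFF, fALFF or ReHo has already given a false positive, so it cannot add to the chance of at least one. Seven maps remain: ALFF, fALFF, ReHo, GMV, CT, CSA and CBF.

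**Independent maps.** 1 − 0.95^7 = 30.2%.

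**Correlated maps.** Simulated equicorrelated two-sided z-tests, 1,000,000 draws, seven tests each at 5%:

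| Assumed correlation | Chance of at least one false result |
|---|---|
| 0 | 30.2% |
| 0.2 | 28.7% |
| 0.5 | 23.0% |
| 0.7 | 17.9% |
| 0.9 | 11.5% |

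**Correlation only within a modality** (three functional, three structural and one perfusion metric, with modalities independent of each other): 27.4% at 0.5, 20.3% at 0.9 and 14.3% at 1.0. The last figure is 1 − 0.95^3.

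**If FC is opened by real change.** The seeding rule does not say whether the significant differences are between-group or within-group, and both two-sample and paired tests are planned. Everyone receives medication and rehabilitation (Basic treatment), so both arms may truly change even if taVNS equals sham. FC would then be an eighth between-group test. With one seed map and independent tests, 1 − 0.95^8 = 33.7%. More seeds would raise it, but their number is not fixed in advance.

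**After correction.** Eight shares: 0.05/8 = 0.00625 per share, and 1 − (1 − 0.00625)^8 = 4.9% if independent.

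**The case against.** **The sentence may mean control within each modality's maps.** It leads into an account of which correction suits which data type, so it can be read as saying that every map is corrected. On that reading it is true, and no overall 5% rate is stated anywhere. This stands, and it is why the point is worded as true at most within each map. The primary family is uncorrected on either reading.

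**Multiplicity may be left to an analysis plan that is not shown.** That would excuse silence. Here the article itself fixes the thresholds and says what they achieve, and it handles multiplicity for the correlations.

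**The aim is preliminary and the sample is admitted to be small.** Both are stated in the Discussion. They would support calling the maps exploratory, but the article calls them primary.

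**Stronger readings that the documents do not support.**
- A reader might put the error at 34% for eight maps, or at 40% by assuming three FC seeds (1 − 0.95^10). Under the global null those FC maps add nothing, because they exist only after an earlier false positive. A figure of 34% or more needs FC to be opened by real change.
- A reader might treat 18% or 19% as a lower bound. It is not; it depends on an assumed correlation near 0.7. Strong correlation is plausible for metrics that share a scan, such as ALFF and fALFF.
- A reader might conclude that CSA should not be primary, since "CSA is thought to be largely determined by the number of cortical minicolumns" and the Discussion predicts nothing for it. The Introduction, however, links sleep deprivation to surface-area change, so its status is the sponsor's choice.
- The Discussion says that naming regions in advance "provides concrete, testable targets for the planned analyses". A reader might infer that those regions go untested and that one regional measure must become the primary. The whole-brain maps do cover the regions; a single regional primary would be a redesign.
- The voxel-level 0.005 is looser than the surface maps' 0.001. Whether it inflates error depends on spatial correlation that the document does not give, so no change to it is asked for here.

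**Conclusion.** The concern holds in this limited form. The stated thresholds control family-wise error at most within each map, and nothing in the article controls it across the primary maps. Under the global null the chance of at least one false between-group primary result is 30% with independent maps, about 23% at correlation 0.5, about 18% at 0.7 and about 11.5% at 0.9. Even the last is more than twice the 5% per map. The figure could reach about 34% or more if real within-group change opens FC.

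The absence of correction across maps is read directly from the text. The size rests on two assumptions: that each map's correction delivers exactly 5%, and that the correlation between metrics is as assumed.

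**What to change.** 1. For any primary between-group claim, apply Holm or Bonferroni across the primary maps. Bonferroni means cluster-level P < 0.05/8 = 0.00625 for each metric. All FC seed maps together form one family that shares the single FC portion, so the number of seeds cannot enlarge the total.
2. Reword the summary sentence in the ASL paragraph to say that the stated thresholds control the family-wise error rate within each map, and add a sentence describing the correction across maps.
3. If the sponsor prefers to keep 0.05 per map, label the maps exploratory and claim no family-wise control across them.

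This should be settled before any analysis by group. It needs wording only and no new data.

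The cost is a stricter bar per map. As an illustration, for one two-sample t-test with 24 per arm, the standardised effect detectable with 80% power rises from about d = 0.83 at 0.05 to d = 1.08 at 0.00625. Cluster inference behaves differently, and 24 per arm assumes no loss although the Sample size calculation expects some, so these values are only a guide. The exploratory option avoids this cost but gives up the confirmatory claim.

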
#### Clinical data analysis

All data in this study will be analyzed using SPSS 26.0 software (IBM Corp., Armonk, NY, USA). Continuous data following a normal distribution are expressed as mean ± standard deviation (Mean ± SD). Intergroup comparisons will be performed using the independent samples t-test, while pre- and post-treatment comparisons within groups will be performed using the paired t-test. Continuous data not following a normal distribution are expressed as median and interquartile range [M(P25, P75)], and intergroup comparisons will be performed using the Mann-Whitney U test. For dynamic observational data involving multiple time points, repeated measures ANOVA will be used. Categorical data will be described using frequencies and percentages (%). Intergroup comparisons for ordinal categorical data will be performed using the chi-square (χ²) test or Fisher’s exact test, while for nominal categorical data, the Kruskal-Wallis H rank-sum test will be used. Furthermore, for the correlation between clinical symptom scales and multimodal MRI indices, Pearson or Spearman correlation analysis will be used, depending on whether the data meet the assumptions of normal distribution and linearity. All statistical tests will be two-sided, and *P* < 0.05 will be considered statistically significant.

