### Sample size calculation

Currently, no precise method exists for calculating the sample size for acupuncture neuroimaging trials. Based on international reviews, a minimum of 12 cases per group is recommended (29, 30). To account for potential data loss and exclusions, this trial will enroll 24 subjects per group, totaling 48 participants.

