### Blinding

To ensure methodological rigor, this trial adopts a single-blind design. Participants will be blinded to group allocation and treated in separate rooms to minimize communication between groups. To assess the effectiveness of the blinding, participants will be asked to guess their group assignment (taVNS group or sham-taVNS group) after the intervention. Due to the specific nature of the taVNS intervention, the therapists cannot be blinded. In contrast, both the outcome assessors and the statistical analysts will remain blinded to the group assignments throughout the study.

Eligible participants will be randomly assigned to the taVNS group or sham-taVNS group in a 1:1 ratio using a computer-generated random sequence. Allocation concealment will be maintained using sequentially numbered, opaque, sealed envelopes prepared by an independent researcher who is not involved in recruitment, intervention, outcome assessment, or data analysis.

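### The tests for categorical data are reversed: chi-square or Fisher is assigned to ordinal data and Kruskal-Wallis to nominal data, so results for nominal variables with three or more categories depend on arbitrary numbering

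*Protocol article*

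**What the plan says.** The rule stands in one sentence of the protocol article, under Clinical data analysis. Its first half reads: "Intergroup comparisons for ordinal categorical data will be performed using the chi-square (χ²) test or Fisher’s exact test". Its second half reads: "while for nominal categorical data, the Kruskal-Wallis H rank-sum test will be used". The same paragraph sets the threshold for every test: "All statistical tests will be two-sided, and *P* < 0.05 will be considered statistically significant". No other section corrects or qualifies the assignment.

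The trial has two arms. Under Sample size calculation, "this trial will enroll 24 subjects per group, totaling 48 participants", and under Blinding, participants are "randomly assigned to the taVNS group or sham-taVNS group in a 1:1 ratio". The one nominal variable that the article expressly plans to collect from participants after treatment is also under Blinding: "participants will be asked to guess their group assignment (taVNS group or sham-taVNS group) after the intervention".

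**The concern.** Kruskal-Wallis compares mean ranks, so it needs categories with a natural order. Nominal categories have none. If the rule is followed, the software ranks whatever numeric codes the data manager happened to assign, and with three or more categories a different numbering gives a different P-value from the same data. The article fixes no numbering.

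Chi-square and Fisher's exact test ignore order. That makes them the natural tests for nominal data. On ordinal data they are legitimate but discard the ordering, which costs power in a trial of 48.

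There is also an effect on binary variables. Because Fisher's exact test is attached to ordinal data, sparse yes/no counts, which are likely with 24 per arm, would go by the letter of the rule to a large-sample rank approximation.

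**Working it through.** The article states no figure on this point, so there is none to reproduce. The check is of the mechanism.

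**Inputs from the protocol article:** two arms, 24 per arm, two-sided threshold 0.05. **Assumed for illustration (not in the article):** all category counts and shares below.

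**1. Nominal variable with three categories A/B/C, counts 12/4/8 v 6/12/6.**

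*Chi-square.* Column totals are 18, 16 and 14, so the expected counts per arm are 9, 8 and 7. χ² = 2 × (3²/9 + 4²/8 + 1²/7) = 2 × (1 + 2 + 0.143) = 6.286 on 2 df, P = 0.043, whatever the numbering.

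*Kruskal-Wallis.* H = [12/(N(N+1))] × Σ(Rᵢ − nᵢ(N+1)/2)²/nᵢ, divided by the tie correction C.
- N = 48, and the expected rank sum per arm is 24 × 24.5 = 588.
- C = 1 − [(18³−18) + (16³−16) + (14³−14)]/(48³−48) = 1 − 12,624/110,544 = 0.886. It is the same for every numbering.
- With W the rank sum of the first arm, H = [12/(48 × 49)] × 2(W − 588)²/24 / 0.886.

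| Order imposed by the codes | Midranks in that order | W | W − 588 | H | P |
|---|---|---|---|---|---|
| A, B, C | 9.5, 26.5, 41.5 | 552 | −36 | 0.622 | 0.43 |
| B, A, C | 8.5, 25.5, 41.5 | 672 | +84 | 3.387 | 0.066 |
| A, C, B | 9.5, 25.5, 40.5 | 480 | −108 | 5.599 | 0.018 |

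The other three numberings are reversals of these and give the same P-values. At the 0.05 threshold, numbering alone decides significance. A second table, 12/4/8 v 5/12/7, behaves alike: 0.274, 0.105 or 0.010 by numbering, against chi-square P = 0.031.

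**2. Power for a nominal variable.** Simulated trials of 24 v 24 with assumed shares 25/50/25% v 45/10/45% give about 82% for chi-square. Kruskal-Wallis gives about 6% under one ordering and about 72 to 74% under the other two. Those two are mirror images for these shares, so the gap between them is simulation error.

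**3. Binary variable.** With two categories and two arms, H = χ² × (N − 1)/N under either coding.
- 16/8 v 9/15: χ² = 4.090 (P = 0.043); H = 4.090 × 47/48 = 4.005 (P = 0.045). Coding is immaterial.
- Sparse case, 4/24 v 0/24: χ² = 4.364, so H = 4.364 × 47/48 = 4.273, P = 0.039. Fisher's two-sided P = 2 × C(24,4)/C(48,4) = 2 × 10,626/194,580 = 0.109.
- 6/24 v 1/24: Kruskal-Wallis P = 0.043, Fisher P = 0.097.

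**4. Ordinal variable.** Simulated power for four levels, assumed equal 25% shares in one arm and a common odds ratio between arms:

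| Odds ratio | Chi-square | Rank-sum test |
|---|---|---|
| 3 | about 36 to 38% | about 53 to 56% |
| 4 | about 54 to 56% | about 72 to 74% |

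The ranges span repeated simulations.

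**The case against.** The strongest reply is that this is a drafting slip with little reach, and most of that stands.

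- **No named endpoint depends on it.** The primary outcomes are MRI measures tested by t-tests. The secondary outcomes (PSQI, NIHSS, ADL, HAMD-17, HAMA-14) are scale scores, for which the same section gives t-tests, Mann-Whitney and repeated-measures ANOVA. Rescue use is nights and total dose. The article names no ordinal categorical endpoint and no nominal endpoint with three or more categories, and it spells out no between-group test of baseline characteristics or adverse events. A reader might infer that the efficacy conclusions are at risk; the document does not support that.
- **Not every nominal P-value depends on coding.** That needs three or more categories. The blinding guess, if recorded as the two named options, gives one P-value under either coding.
- **The P-values are not meaningless.** Under a coding fixed beforehand, Kruskal-Wallis keeps its false-positive rate (4.8 to 5.3% in simulation under no difference). The fault is dependence on an arbitrary choice, and erratic power.
- **The 6% power is the worst ordering**, on shares that happen to cancel under it. It must be read with the 72 to 74% for the others.
- **Chi-square on ordinal data is inefficient, not invalid.**

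What does not stand is that the sentence can be left because an analyst would ignore it. It is a stated rule, not a detail left to the analysis plan. Following it gives coding-dependent results for multi-category nominal variables; ignoring it is a departure from the published plan.

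**Conclusion.** The point holds. The sentence assigns each family of tests to the wrong kind of data, and this follows from the text without any assumption. The size of the effect rests on illustrative tables and assumed shares at the trial's 24 per arm, because the article gives no categorical data:

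- for nominal variables with three or more categories, the P-value can cross 0.05 on numbering alone;
- for sparse binary variables, the exact test is not the one assigned;
- for ordinal variables, the loss is some 15 to 20 percentage points of power in the scenarios tried.

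The reach is limited to categorical summaries: the blinding check, and any comparison of baseline characteristics or adverse events that is made. The main efficacy analyses are untouched. Severity is minor to should-fix.

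**What to change.** Exchange the words *ordinal* and *nominal* in that sentence. Nominal data, binary variables included, are then compared by chi-square or Fisher's exact test, with Fisher available for sparse counts. Ordinal data are compared by the rank-sum test. With two arms this can be named as Wilcoxon-Mann-Whitney, to which Kruskal-Wallis is equivalent (without continuity correction the two give the same P-value), so the exchange alone is enough.

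The cost is one sentence, changed before analysis and noted as a correction. It needs no extra data, patients or procedures.
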